# Influence of an exercise program on cardiac remodeling and functional capacity in patients with stroke (CRONuS trial): study protocol for a randomized controlled trial

**DOI:** 10.1186/s13063-019-3328-1

**Published:** 2019-05-28

**Keywords:** Stroke, Physical exercise, Cardiovascular rehabilitation, Echocardiography, Functional capacity

## Abstract

**Background:**

Cardiovascular rehabilitation is one of the treatment options for post-stroke individuals in order to improve functional independence in activities of daily life and reduce energy expenditure. The aim of this trial is to evaluate the effect of an exercise program on the echocardiographic variables, functional capacity, inflammatory response, neurological status, nutritional status, cardiologic evaluation, and quality of life of patients after stroke.

**Methods/design:**

This is a randomized controlled trial including patients with ischemic stroke in the chronic phase. The patients will be evaluated at the beginning of the study and after 16 weeks. This will include clinical and physical evaluation, 6-min walk test, neurological assessment, nutritional assessment, ambulatory blood pressure monitoring, transthoracic echocardiography, and assessment of the quality of life. The sample size has been determined as 40 patients, who will be divided into two groups: control group (CG; *n* = 20) and intervention group (IG; n = 20). The CG will undergo conventional physiotherapy for 45 min, three times a week, up to 16 weeks, while the IG will be put on a cardiovascular rehabilitation program consisting of heating, aerobic exercise, and muscle strengthening for 45 min, three times a week, for 16 weeks. The primary endpoint will be functional capacity following a 6-min walk test (delta maxVO_2_) and morphofunctional echocardiographic variables (indexed left ventricular mass) before and after the intervention.

**Discussion:**

We expect to observe an improvement in cardiac structural and functional abnormalities in the IG, on echocardiography and biochemical examination, and that the improvement of these parameters after cardiovascular rehabilitation will have a favorable impact on the functional capacity and quality of life of patients after stroke.

**Trial registration:**

REBEC, RBR-4wk4b3. Registered on 19 September 2016.

**Electronic supplementary material:**

The online version of this article (10.1186/s13063-019-3328-1) contains supplementary material, which is available to authorized users.

## Background

Worldwide, stroke is a leading cause of morbidity and mortality, affecting around 200,000 individuals annually. In addition, it is a major cause of chronic disability in adults, with major impacts on the health and quality of life of the affected population [1, 2].

Stroke is defined as an episode of sudden neurological dysfunction of ischemic or hemorrhagic origin, with persistent clinical symptoms over an hour and evidence of demonstrable lesion on imaging tests [3]. Pathologically, stroke can be defined as brain cell death resulting from a prolonged ischemic event [4].

The incidence of stroke is greater in men aged 45–85 years and in women over 85 years. The major risk factors for ischemic stroke are increased blood pressure, diabetes mellitus (DM), cardiac arrhythmias, dyslipidemia, smoking, physical inactivity, genetic or family history of stroke, chronic kidney disease, and sleep apnea syndrome [5]. The etiology of hemorrhagic stroke can be primary (hypertension or amyloid angiopathy) or secondary to vascular malformations, such as aneurysm, cavernous angioma, venous angioma, venous sinus thrombosis, vasculopathies, and central nervous system tumors, among others [6].

After a stroke, individuals require long periods of rehabilitation to increase their functional capacity and to minimize the sequelae resulting from brain injury [7, 8]. In the chronic phase of stroke, 62% of patients need assistance in activities of daily living (ADL), and less than half of patients are able to perform independent walking, which is the most disabling outcome of the disease, decreasing their overall physical capacity [9–11].

Inactivity through reduced mobility and low levels of aerobic capacity after stroke result in several dysfunctions, such as reduction in cardiorespiratory fitness, loss of 20% of the cross-sectional area of the muscle, and an increase of about 25% of intramuscular fat, leading to osteoporosis. There is also the circulatory involvement of the lower extremities, as well as psychological effects such as apathy and depression [8–12]. In association with other comorbidities such as DM, hypertension, and increased body mass index, the risk of associated cardiovascular events may increase in addition to recurrence of stroke [13].

In conventional rehabilitation after stroke, the goal is to achieve maximum functional recovery [14, 15]. However, approximately 75% of individuals have associated heart disease after experiencing a stroke, thereby reducing their functional capacity to perform ADL [16–18]. Immobility after stroke results in resistance to physical exercise, including ADL [19, 20].

Several studies have reported that the maximum oxygen capacity (VO_2max_), defined as the critical (peak) oxygen capacity during aerobic activity, is reduced to 10–17 ml/kg/ min in the first 30 days after stroke, and does not reach values > 20 ml/kg/min after 6 months of the event [21–26]. VO_2max_ values after stroke decrease by 25–45% compared to healthy individuals in the same age group, which may interfere with the rehabilitation process and functional prognosis in the long term [27, 28].

Therefore, cardiorespiratory rehabilitation aims to provide greater functional independence during ADL with lower energy expenditure [28]. Several authors have reported that conventional rehabilitation is effective in improving the functional independence of individuals after stroke, but cardiorespiratory rehabilitation can restore aerobic capacity, reduce energy expenditure to perform ADL, and reduce the occurrence of cardiac events and recurrence of stroke [14, 15, 19, 20, 26–28]. However, the type, frequency, and appropriate method to achieve these goals during cardiorespiratory rehabilitation remain unclear in the literature. Hence, this study has clinical importance.

The main aim of this study is to evaluate the effect of a cardiovascular rehabilitation program on morphofunctional echocardiographic variables and functional capacity in patients with chronic ischemic stroke. In addition, we will assess the effects of cardiovascular rehabilitation on the inflammatory response, neurological status, nutritional status, cardiologic evaluation, and quality of life. We also aim to evaluate the association between clinical variables (age, anthropometric data, mean systolic blood pressure, 24-h diastolic blood pressure, magnitude of the nocturnal decrease in systolic blood pressure, diastolic and pulse pressure, use of antihypertensive medications) and echocardiographic variables and VO_2max_.

## Methods/design

### Design

This single-center, randomized, single-blind, parallel group study of 40 patients with stroke will be conducted in accordance with the Consolidated Standards of Reporting Trials (CONSORT) 2010. A flow diagram of the study is presented in Fig. 1.

**Fig. 1 Fig1:**
[figure not shown]
Study flow diagram

### Patient population

Participants were recruited from the Cardiac RemOdeliNg and functional capacity in patients with Stroke (CRONuS) trial, a single-center, randomized, single-blinded study of cardiac rehabilitation in 40 individuals with stroke at UNESP – University Estadual Paulista, Botucatu Medical School, Brazil.

### Inclusion criteria

Participants older than 18 years of either sex, with a history of ischemic stroke, modified Rankin scale (mRS) ≤ 2, and currently in the chronic phase of stroke (6 to 12 months after onset of symptoms), but clinically stable to participate in the study after discharge from hospital [28].

### Exclusion criteria

Patients with hemorrhagic stroke, mRS > 2, uncontrolled hypertension (systolic blood pressure ≥ 150 mmHg), history of angina in the last 3 months, uncontrolled epilepsy, persistent or permanent atrial fibrillation and/or using a pacemaker, presence of valvulopathies such as mitral and/or aortic stenosis, presence of grade IV heart failure, stage D chronic obstructive pulmonary disease, and life expectancy < 6 months.

## Randomization and blinding

The concealed randomization schedule will be established using a computer-generated random number sequence and maintained by an offsite investigator who will not be involved with the enrolment nor the assessment of study participants. A second research assistant will sequentially open consecutively numbered, randomly ordered, opaque envelopes containing the group allocation (in a 1:1 ratio) after baseline assessment. The patients will be evaluated before the beginning of the first session and a week after the last session by a blinded investigator.

## Intervention

Frequency, duration, intensity, and supervision standards will be established for the implementation and maintenance of the cardiovascular rehabilitation program, which proposes approximately 45 min of exercises, three times a week, for 16 weeks (48 sessions), consisting of the following three phases [28–30]:Heating: light walk for a duration of 5 to 10 min.Aerobic exercises: 30 min of aerobic exercise on the treadmill without programmed increase in speed, compatible with walking ability of the patient, and achieving approximately 40 to 80% of maximum heart rate reserve. It is calculated by the Karvonen formula for target heart rate where Target heart rate = [% intensity × (Maximum HR − Resting HR)] + Resting HR; it can be readjusted according to the sessions and is progressive. This phase will take place under professional supervision.Muscle cooling: static stretching of the hamstrings, quadriceps, sural triceps, and hip adductors for 5–10 min.

The protocol will include physiologic monitoring of blood pressure, heart rate, respiratory rate, peripheral oxygen saturation, and perceived exertion (modified BORG scale). The individual will also be instructed to stop the activity if any discomfort is felt.

Patients in the control group will receive conventional outpatient physiotherapeutic care at the Clinical Hospital, UNESP—University Estadual Paulista, Botucatu Medical School, Brazil. No changes will be made to the standard hospital protocol in terms of the content, time, or duration of the session. The protocol will be based on physiotherapeutic intervention guided by the National Institute for Health and Care Excellence (2013), with exercises consisting of 10 min of stretching exercises for the lower limbs, 15 min of strengthening exercises with emphasis on core, knee extensors and flexors, plantar flexors and dorsiflexors, and 20 min of gait training with obstacles and variabile speed. Patients will wear orthoses for gait training physical therapy three times a week for 16 weeks, for 48 sessions in total.

### Primary outcome measures

The primary endpoint will be measured as functional capacity following a 6-min walk test (delta maxVO_2_) and morphofunctional echocardiographic variables (indexed left ventricular mass) before and after the intervention.

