## Procedures (template)

Individuals diagnosed with ischemic stroke will be sent to the rehabilitation center after discharge from the hospital. All individuals with ischemic stroke confirmed by a computed tomography (CT) or magnetic resonance imaging (MRI) scan will be invited to participate in the study. The patient, a family member, or guardian must sign an informed consent form. The individuals will then be evaluated for their clinical and neurological status. Individuals will be assessed using the National Institutes of Health Stroke Scale (NIHSS), the Barthel Index of ADL, and the mRS. The aerobic capacity will be evaluated by VO_2max_, functional capacity will be assessed by a 6-min walk test, nutritional status by electric bioimpedance, cardiologic examination by ecocardiography, and laboratory exams and the quality of life will be based on the European Quality of Life Scale. The tests will be performed by an investigator who is blinded to the treatment that the patient received before the first session and a week after the last session. After the clinical screening, they will be randomized into the following two groups: 1) control group (CG; 20 patients); 2) intervention group (IG; 20 patients) (Fig. 2).

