### Evaluation of functional capacity

#### Aerobic capacity

A maximum stress test will be used to obtain VO_2max_, peak work rate, and anaerobic ventilatory threshold. The heart rate and resting blood pressure will be measured before and after the exercise. The stress test will be based on a modified Bruce protocol that uses a time-dependent slope [31]. The protocol will be based on the study by Tang et al. [32], which used 5, 10, or 15-watt work rates for a total test duration of between 8 and 10 min.

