#### Six-minute walk test

The 6-min walk test establishes functional fitness of gait through performance and physical resistance. The test measures the maximum distance reached along a course of 30 m in 6 min. The expected distance to be reached by the patient will be calculated based on age, sex, weight, and height [33, 34]. Equipment required for the test include a stopwatch, cones for circuit delimitation, sphygmomanometer, stethoscope, and pulse oximeter. According to the protocol proposed by the American Thoracic Society guidelines, the evaluator should not walk with the patient, but may walk behind the patient if necessary to carry the oxygen source or in case the patient loses balance. During the test, encouraging (standardized) phrases should be used over time. Vital signs are checked at the beginning and end of the test [35].

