## Sample size estimation

The sample size was calculated to match primary outcome with sample size estimation.

According to Framingham data [47], an increase of 20 g/m^2.7^ in left ventricular mass index presents a hazard ratio to hard end points of about 1.5; in this study the standard deviation was 30 g/m^2.7^. To detect these clinically significant differences between groups, with a fixed alpha error of 0.05 and beta error of 0.20, 37 patients per group will be needed.

According to the cohort of Presher et al. [48], an increase of 66 m in the 6-min walking test discriminates survivors from non- survivors among heart failure patients; in that study the standard deviation was 90 m. To detect these clinically significant differences between groups, with a fixed alpha error of 0.05 and beta error of 0.20, 31 patients per group will be needed.

Therefore, we will study 40 patients per group to detect these differences properly.

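### The functional-capacity primary endpoint is named as change in maximal VO2 from a 6-min walk test, but that test yields a distance, VO2max comes from a different test, and this endpoint is sized in metres

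*Protocol article*

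**What the plan says.** Under Primary outcome measures, the protocol article names two components. One is left ventricular mass index. The other is "functional capacity following a 6-min walk test (delta maxVO_2"). The abstract has the same pairing: "The primary endpoint will be functional capacity following a 6-min walk test (delta maxVO_2").

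Other sections describe the two exercise measures as follows.

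- **Six-minute walk test:** "The test measures the maximum distance reached along a course of 30 m in 6 min". The apparatus is listed: "Equipment required for the test include a stopwatch, cones for circuit delimitation, sphygmomanometer, stethoscope, and pulse oximeter". The only derived quantity mentioned is an expected distance.
- **Aerobic capacity:** "A maximum stress test will be used to obtain" VO2max, together with peak work rate and the ventilatory threshold.
- **Procedures (template):** aerobic capacity is assigned to VO2max, and "functional capacity will be assessed by a 6-min walk test".
- **Discussion:** walk distance and VO2max appear as separate expected improvements.
- **Sample size estimation:** the section opens by saying that the calculation corresponds to the primary outcome. For functional capacity it then relies on a heart-failure cohort in which "an increase of 66 m in the 6-min walking test discriminates survivors from" non-survivors, with an SD of 90 m, giving 31 per group. For left ventricular mass index it uses 20 g/m^2.7 with an SD of 30, giving 37 per group.

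**The concern.** The definition joins the name of one test to the variable of another. Read literally, it calls for a quantity that the walk test, as described, does not yield. Read loosely, it could mean change in walk distance (m) or change in stress-test VO2max (ml/kg/min).

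Two things are at stake.

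- **Selection.** Secondary outcome measures lists inflammatory, neurological, nutritional, cardiologic and quality-of-life outcomes. Neither walk distance nor VO2max is named there, so whichever is not the primary has no stated rank. Either could be called the primary after the data are seen, and the text would not contradict it.
- **Power.** The stated type II error of 0.20 for this endpoint was computed in metres. If VO2max is the primary variable, the plan makes no power statement for it.

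**Working it through.** **1. Which variable, which test, which unit**

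| Section | Test | Variable | Unit |
|---|---|---|---|
| Abstract; Primary outcome measures | 6-min walk | change in maximal VO2 | not stated |
| Six-minute walk test | 6-min walk | distance | m |
| Aerobic capacity | maximal stress test | VO2max | ml/kg/min (as used in Background) |
| Procedures (template) | both, listed separately | VO2max for aerobic capacity, walk test for functional capacity | not stated |
| Sample size estimation | 6-min walk | distance | m |

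The first row agrees with none of the others. Nothing bridges the gap: the walk-test apparatus includes no gas analysis, and no equation converts distance into VO2.

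**2. Reproducing the stated size for this endpoint**

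Inputs from Sample size estimation: difference 66 m, SD 90 m, alpha 0.05, power 0.80. Allocation is 1:1 (Randomization and blinding). A two-sided test is assumed because sidedness is not stated.

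Normal approximation: n per group = 2 × (1.960 + 0.842)² × (90/66)² = 2 × 7.85 × 1.860 = 29.2, rounded up to 30.

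Two-sample t-test: 30.18, rounded up to **31**, the stated figure. A one-sided test gives 23 to 24 and does not reproduce it.

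**3. The other primary, as a check**

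Left ventricular mass index: 2 × 7.85 × (30/20)² = 35.3, rounded up to 36. The t-test gives 36.31, rounded up to **37**, as stated. Here variable and calculation agree.

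**4. What can be said about power if VO2max is the primary**

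The protocol gives no target difference and no SD for VO2max, so no sample size or power can be computed. Only the detectable standardised difference at 80% power, two-sided 0.05, can be given. It is shown for two group sizes because Sample size estimation says 40 per group while the abstract and Procedures say 20 per group; that conflict is a separate matter.

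Normal approximation: d = (1.960 + 0.842) × √(2/n).

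| n per group | d, normal | d, t-test | Detectable VO2 difference, assumed SD of change 2 to 6 ml/kg/min |
|---|---|---|---|
| 40 | 0.63 | 0.63 | about 1.3 to 3.8 ml/kg/min |
| 20 | 0.89 | 0.91 | about 1.8 to 5.5 ml/kg/min |

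The SD range is an assumption made only to show scale. For comparison, power for 66 m of walk distance by t-test is about 90% with 40 per group and about 62% with 20.

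**The case against.** The best defence is that the definition does name one variable, twice, and that variable is maximal VO2. Background includes VO2max among the study aims, and the heading for evaluation of functional capacity covers both the stress test and the walk test. On that reading the variable is settled and only the test is misattributed. This has some force: the text does not dictate that walk distance must be the primary. It does not remove the fault, because Procedures assigns functional capacity to the walk test and the sizing is in metres.

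It might also be said that VO2 could be estimated from walk distance, or that a condensed article leaves such detail to the full protocol. No section mentions an estimate, the Aerobic capacity section takes VO2max from elsewhere, and the calculation would still be in another unit. The fault is conflicting text, not missing detail.

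Three stronger readings are tempting and are not supported:

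- **That the whole trial is sized in metres.** It is also sized on left ventricular mass index, which gives the larger requirement (37 against 31 per group).
- **That three primary tests raise the false-positive risk to 1 − 0.95³ = 14.3%, against 1 − 0.95² = 9.8% for two.** The document never plans three primary tests. The 14.3% assumes independence, which is implausible for two exercise measures in the same patients.
- **That VO2 change will be biased by a shifting stress-test method.** The Aerobic capacity section refers both to a modified Bruce scheme and to a cited study "which used 5, 10, or 15-watt work rates for a total test duration of between 8 and 10 min". How these fit together depends on references not at hand, and nothing says that the method may differ between patients or visits.

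**Conclusion.** The point holds for the functional-capacity primary. Variable, test and sizing unit do not match, and no section reconciles them. The stated 31 per group is arithmetically correct under a two-sided t-test, but it supports 80% power for a 66 m difference in walk distance only. Power for change in VO2max is unstated and cannot be derived from the document. The mass-index primary is not affected.

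Because the defect lies in the definition of a primary endpoint and leaves the choice of variable open until results are known, it needs correcting. Its size is best expressed as an undefined primary variable with a power claim that may not apply to it, not as a particular inflation of the type I error rate. The conclusion rests on the text alone; the two-sided test and the illustrative VO2 SDs affect only the figures in the working.

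**What to change.** Before any outcome data are examined, state in the abstract and in Primary outcome measures one functional-capacity variable, the test that produces it and its unit, and list the other measure as secondary. Either choice is open:

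- **Walk distance (m) as primary.** Replace the VO2 term in the definition. The existing 66 m and 90 m calculation then applies as it stands.
- **Stress-test VO2max (ml/kg/min) as primary.** Remove the reference to the walk test from the definition. Then either replace the calculation with one using a justified difference and SD in ml/kg/min, or say plainly that the power claim does not cover this endpoint.

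Neither option adds a procedure, since both tests are already planned. The cost is more than editorial: the trial is described as ongoing, so this is a mid-trial clarification of a primary endpoint. It should be dated, justified and recorded as made without knowledge of outcome data, and the registration entry should be checked for agreement. The VO2max option also needs planning inputs that the document does not contain.

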### Secondary outcome measures

The secondary endpoints will be inflammatory responses, neurological status, nutritional status, cardiologic evaluation, and quality of life.

### Adverse effects

Adverse effects, frequency, duration, exercise intensity, and/or other relevant events will be recorded every week.

